## Abstract

**Background:**

Fear of cancer recurrence (FCR) is common in people affected by breast cancer. FCR is associated with increased health service and medication use, anxiety, depression and reduced quality of life. Existing interventions for FCR are time and resource intensive, making implementation in a National Health Service (NHS) setting challenging. To effectively manage FCR in current clinical practice, less intensive FCR interventions are required. Mini-AFTERc is a structured 30-min counselling intervention delivered over the telephone and is designed to normalise moderate FCR levels by targeting unhelpful behaviours and misconceptions about cancer recurrence.

This multi-centre non-randomised controlled pilot trial will investigate the feasibility of delivering the Mini-AFTERc intervention, its acceptability and usefulness, in relation to specialist breast cancer nurses (SBCNs) and patients. This protocol describes the rationale, methods and analysis plan for this pilot trial of the Mini-AFTERc intervention in everyday practice.

**Methods:**

This study will run in four breast cancer centres in NHS Scotland, two intervention and two control centres. SBCNs at intervention centres will be trained to deliver the Mini-AFTERc intervention. Female patients who have completed primary breast cancer treatment in the previous 6 months will be screened for moderate FCR (FCR4 score: 10‑14). Participants at intervention centres will receive the Mini-AFTERc intervention within 2 weeks of recruitment. SBCNs will audio record the intervention telephone discussions with participants. Fidelity of intervention implementation will be assessed from audio recordings. All participants will complete three separate follow-up questionnaires assessing changes in FCR, anxiety, depression and quality of life over 3 months. Normalisation process theory (NPT) will form the framework for semi-structured interviews with 20% of patients and all SBCNs. Interviews will explore participants’ experience of the study, acceptability and usefulness of the intervention and factors influencing implementation within clinical practice. The ADePT process will be adopted to systematically problem solve and refine the trial design.

**Discussion:**

Findings will provide evidence for the potential effectiveness, fidelity, acceptability and practicality of the Mini-AFTERc intervention, and will inform the design and development of a large randomised controlled trial (RCT).

**Trial registration:**

ClinicalTrials.gov: NCT0376382. Registered 4th December 2018, https://clinicaltrials.gov/ct2/show/NCT03763825

## Background

Fear of cancer recurrence (FCR) is prevalent amongst people affected by breast cancer, with 60% or higher claiming they want to speak with their cancer care team to discuss their fears [1]. Fear of cancer recurrence is defined as “Fear, worry, or concern relating to the possibility that cancer will come back or progress” [2]. FCR is an understandable reaction to surviving a serious illness; however, when it becomes severe it can produce unwanted effects including loss of concentration, lowered quality of life, propensity to depression as well as increased health service utilisation, medication and over frequent self-examination [3–6]. FCR results from the activation of certain cognitions, beliefs and emotions that an individual acquires following cancer diagnosis and treatment [7]. Therefore, psychological interventions are needed to assist patients to better cope with FCR [6].

Intensive psychological interventions for FCR are available, including ConquerFear [8], SWORD [9] and AFTER [10]. However, such interventions are designed for those with ‘severe’ FCR and are highly resource and time intensive. In the UK, a national lack of funding and highly trained mental health professionals (psychologists, psychiatrists, etc.) across the National Health Service (NHS) [11] would make implementing such intensive interventions difficult. Nevertheless, some form of intervention is crucial as once FCR becomes severe, it is particularly challenging to reduce [6]. Interventions may also reduce costs and pressure on specialist services because patients with high FCR use more specialist services [12, 13].

A recent randomised control trial of an online-only intervention (CAREST-trial) to support individuals to manage elevated FCR found that the intervention produced no significant reduction in FCR [14]. This finding demonstrates that online self-management approaches may not effectively manage FCR and highlights the potential need for interpersonal interaction to improve FCR. A review of FCR interventions delivered by non-mental health professionals concluded that professionals other than psychologists can deliver psychological and counselling interventions to reduce FCR in patients affected by cancer [15]. Specialist cancer nurses are potentially ideal candidates to deliver FCR interventions as they provide psychological support to patients from the point of cancer diagnosis onwards [15]. Given this evidence, it is important that further research is undertaken to develop and test less intensive FCR interventions that can be delivered by non-mental health professionals and are suitable to implement into current clinical practice.

The Mini-AFTERc intervention is a cognitive behavioural intervention based on the self-regulation model (SRM) of illness cognitions [16]. It is a less intensive version of the AFTER intervention [10] and is designed to be delivered by trained specialist cancer nurses in approximately 30 min [17]. Mini-AFTERc aims to reduce FCR in people affected by cancer by targeting inappropriate or unhelpful behaviours (e.g. twice daily self-examination), and misconceptions about cancer recurrence. A common example of misconception is that patients will interpret new symptoms or sensation, such as acute pain, numbness or tingling, as cancer recurrence. Before the cancer diagnosis, patients may have interpreted these new experiences as harmless, but post-diagnosis patients may assume that they have sinister connotations. The intervention does not intend to dispel fears entirely or to reduce unduly attention to symptom change and appropriate self-examination behaviours.

A feasibility study of the Mini-AFTERc intervention was conducted within one breast service in NHS Scotland [17]. A sample of 16 patients who had completed breast cancer treatment reported a significant decrease in FCR at 1 week after the intervention was delivered. In this setting, specialist breast cancer nurses (SBCNs) who were trained in and delivered Mini-AFTERc found the intervention manageable and easy to follow. SBCNs also believed the intervention may be useful for reducing the demand on their time and resources by addressing FCR before it becomes severe [17]. Additionally, a mixed-methods study with 90 UK-based SBCNs aimed to determine the acceptability of implementing the Mini-AFTERc intervention into current practice [18]. SBCNs were asked how FCR was currently identified, assessed and supported, and their willingness to implement the Mini-AFTERc, via an online survey and semi-structured interviews. FCR was reported to be an important issue by SBCNs, but their reported practices to identify, assess and support FCR were highly variable. SBCNs viewed the Mini-AFTERc intervention favourably and believed it would enhance their skills in the managing FCR [18]. Following the favourable outcomes of these studies, additional research is required to assess the feasibility and acceptability of the Mini-AFTERc intervention amongst a larger sample of patients.

## Methods

### Aim and objectives

The aim of this pilot trial is to investigate the acceptability and feasibility of delivering the Mini-AFTERc intervention in every day clinical practice. The objectives are as follows:
To develop a procedure for training SBCNs in the delivery of the Mini-AFTERc intervention.To assess the acceptability of the Mini-AFTERc intervention for SBCNs and patients and the feasibility of introducing the intervention into current NHS service provision.To apply a formal decision-making framework to identify potential difficulties in the implementation of the pilot trial and appraise solutions prior to the development of a full-randomised control trial.

### The Mini-AFTERc intervention

The Mini-AFTERc intervention is a manualised structured discussion plan comprising of five topics which are discussed during a 30-min telephone discussion. The Mini-AFTERc intervention was designed to target specifically the antecedents within the cognitive formulation of FCR developed by Lee-Jones et al. [7].

The first stage of the Mini-AFTERc intervention is assessment. The assessment stage aims to establish an understanding of the participant’s experiences and symptoms of FCR and to tailor the subsequent intervention discussion to the participant’s needs. Assessment processes are common to all cognitive behavioural-based interventions [19]. The Mini-AFTERc assessment is structured (Fig. 1) to ensure that all aspects of the four primary discussion topics (family, thoughts and feelings, expectations, return of cancer) are raised with the participant. This allows the individual delivering the intervention to prioritise and target one or two of the discussion topics for further detailed discussion.

**Fig. 1 Fig1:**
[figure not shown]
Topics covered during the Mini-AFTERc assessment phase

Family is the first detailed discussion topic of the Mini-AFTERc intervention. Social constraints have been shown to increase FCR [20] and present a possible pathway to FCR development, therefore this topic focuses on communication processes with the participant’s family and friends. The quality of their participant’s relationship with family and friends is assessed and whether the participant has an individual who they can have open discussions with about their thoughts and feelings (a confidante). The individual delivering the intervention may encourage the participant to have more open discussion with family and friends about how they are feeling and/or to explore other means of social support (e.g. cancer support groups).

The second detailed discussion topic is thoughts and feelings. This topic concentrates on the identification of symptoms experienced during treatment and those after treatment completion. This phenomenon has been identified previously in people affected by breast cancer [21]. Participants who associate symptoms (i.e. ‘triggers’) as indicators of cancer returning are invited to describe these symptoms in greater detail. The individual delivering the intervention may normalise the participants’ experiences (i.e. “many people experience these symptoms after treatment”); an approach which has been used effectively in the field of psychosis [22]. They may also provide additional information to persuade the participant that such symptoms are not necessarily indicative of cancer returning [23].

The third detailed discussion topic is expectations. This topic invites participants to relate their concerns about follow-up visits, scans and self-awareness/checking. Previous evidence indicates that expectations about the outcome of upcoming out-patient visits [24] and/or self-examination behaviours [21] may heighten FCR. Some individuals may engage in these behaviours as an FCR management strategy, conforming to a cognitive behavioural model. The individual delivering the intervention may assist participants to understand their reactions to their behaviour [19] and recommend graded behaviour change.

The fourth discussion topic is return of cancer and focuses on the participants thought about the future. The individual delivering the intervention may normalise the participants’ concerns about the future. Through a process of brief graded exposure [25] to the possibility of the cancer returning, they may encourage the participant to express their anxieties openly.

The Mini-AFTERc discussion concludes with a short summary of issues covered and suggested recommendations or action plans discussed during the telephone conversation. Participants will also be given the opportunity to ask any questions they may have. Thirty minutes is considered the optimal time required to fully address two of the discussion topics. Nurses will be advised to complete the discussion within 30 min however this is not categorical. Nurses will be encouraged to use their discretion to extend the discussion beyond 30 min. The duration of discussions will be recorded as part of this study. If the nurses have any outstanding concerns about a patient after their discussion that they think require more extensive discussion then they are advised to refer the patient for additional psychological support through the usual pathway at their cancer centre.

Patient FCR will be monitored after the intervention has been delivered as part of this study using a self-report questionnaire. Any patients who display increasing FCR will be offered additional support at the end of the study. This support may include one-to-one counselling at the breast cancer centre or the offer of a referral to specialist psychological services. All referrals and offers of additional support will be recorded as part of this pilot trial.

### Trial design

This study is a non-randomised controlled pilot trial conducted within four breast cancer centres in NHS Scotland. The Mini-AFTERc intervention will be delivered at two of the sites in addition to standard care and compared to standard care alone delivered at the two control sites. The selection of cancer centres was dependant on the proximity of the research institutions and local knowledge of service provision. Guidance in relation to breast cancer follow-up after primary diagnosis is inconsistent [18]. Consequently, standard care (i.e. follow-up and support for patients once they have completed primary cancer treatment) can vary between cancer centres, in terms of timing and types of support offered. SBCNs at the intervention sites will be recruited and trained to deliver the Mini-AFTERc intervention using a pre-determined training programme, which will be further developed and refined with feedback from participating SBCNs during this trial.

Participants will be recruited from hospital clinics and over the telephone. Participants from intervention centres will receive an intervention telephone call within 2 weeks of recruitment. All participants (intervention and control) will be asked to report their FCR, mood and quality of life over a three-month follow-up period (Fig. 2). A bespoke smartphone application, already designed to collection questionnaire responses form patients, will also be tested as part of this pilot trial.

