### Phase 2: Intervention delivery and data collection

#### Eligibility and recruitment

Mini-AFTERc is designed for patients with *moderate* FCR, therefore consented patients will complete the fear of cancer recurrence 4-item (FCR4) measure [27] to determine their eligibility (score range: 10‑14). The FCR4 has been previously shown to be reliable (*α* 0.93, 95% CI 0.91‑0.94) [27]. Any patient who score > 14 (i.e. high) on the FCR4 will be offered a referral onto psychological support services, in line with standard practice at each cancer centre. Additional patient eligibility criteria for screening are broad to ensure external validity of the sample. Patients will be eligible for screening if (1) they have completed their primary cancer treatment for breast cancer, (2) are cancer-free, (3) are female, (4) are aged 18 or over and (5) their responsible clinician agrees to their participation. Patients will be ineligible for screening if they have not completed their cancer treatment, are not cancer-free, are male and/or are receiving treatment for a diagnosed psychotic disorder that is known to the cancer service.

Potential participants will be identified in the cancer centres via patient appointment systems. A one-page study information letter will be sent to potential participants prior to their follow-up appointment or end of treatment review. There are two potential recruitment and consent processes:

*Process 1*. Participants attending in person will be invited to speak directly with a researcher about the study in the clinic. This meeting will provide study information and consent will be taken to participate in the trial.

*Process 2*. Participants not attending in person will have the study introduced by their cancer care team and be asked to consent to their contact details being shared with the research team. The researchers will contact potential participants to discuss the trial, provide additional information and consent. All study information and consent forms will be mailed. Consent forms will be required to be returned before participants can continue in the study.

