#### Screening and baseline assessment

Screening will be conducted with the fear of cancer recurrence 4-item (FCR4) measure [27]. Participant demographical information, including age (in years), cancer treatments received, education, employment and living situation, will also be collected during screening but eligibility will not depend on this information. A score of ≥ 10 and < 15 in the FCR4 is defined as ‘moderate’ FCR. Patients will be excluded from the trial if they score ‘low’ (< 10) or ‘high’ (≥ 15) on the FCR4. It is anticipated that 3 in 10 patients will obtain an FCR4 scoring in the moderate range (60th percentile) therefore approximately 440 participants will be required to be screened to obtain the required sample of 130. If eligible after screening, participants will be asked to complete the Hospital Anxiety and Depression Scale (HADS) [28] and the Euro-Qol 5-dimension health-related quality of life measure (EQ-5D-5 L) [29] at baseline. All initial screening and baseline data collection will be completed by the researcher and the participant either face to face or over the telephone.

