### Phase 3: Evaluation

#### Quantitative analysis

Data collected from self-report questionnaires will be quantitatively analysed using the STATA software [32]. A detailed CONSORT diagram will be completed with fully annotated reasons for withdrawal from the study and follow-up rates where possible. This will also include numbers referred onto further specialist services during the study. Descriptive statistics of questionnaire data will be reported and inferential statistics, including mixed regression modelling, will investigate outcome variable associations. Growth curve analysis (linear and polynomial parameters), will be performed using MPlus [33] to calculate the fear of cancer recurrence trajectory and intercept link intervention and control groups. Interclass correlation coefficient (ICC) will also be determined to estimate the potential power required for future trials, based on the number of clusters and sample size per cluster. The Monte Carlo modelling approach within MPlus, advanced by Bolger and Laurenceau [34], will be utilised to determine the sample size required to estimate for a moderate effect of the difference in trajectory (i.e. slope coefficient) between intervention and control groups with covariates (age, treatment experience, disease severity). Alpha set to 0.05 (2-sided). Analysis will not be blinded and will be conducted by the local research teams (St Andrews and Stirling Universities) who will seek advice from a divisional statistician (St Andrews).

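### Arm is set by centre and post-treatment care can vary by centre, yet the covariates named for the FCR trajectory do not clearly include time since treatment ended, and routine support is not named for collection

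*Protocol article*

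**What the plan says.** All references are to the protocol article.

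- **Allocation (Trial design).** Arm is fixed by centre: "The Mini-AFTERc intervention will be delivered at two of the sites in addition to standard care and compared to standard care alone". On how centres were chosen: "The selection of cancer centres was dependant on the proximity of the research institutions and local knowledge of service provision".
- **Care by centre (Trial design).** Follow-up and support after primary treatment "can vary between cancer centres, in terms of timing and types of support offered".
- **Point of entry (Eligibility and recruitment).** The information letter goes out "prior to their follow-up appointment or end of treatment review".
- **Time window.** The Abstract restricts screening to women who finished primary treatment within the last 6 months. The criteria under Eligibility and recruitment require completed treatment but give no window.
- **Baseline data (Screening and baseline assessment).** "Participant demographical information, including age (in years), cancer treatments received, education, employment and living situation, will also be collected during screening".
- **Covariates (Quantitative analysis).** The simulation of the sample size needed to detect a difference in slope between the groups uses "covariates (age, treatment experience, disease severity").
- **Support data.** The section on the Mini-AFTERc intervention states: "All referrals and offers of additional support will be recorded as part of this pilot trial". Quantitative analysis adds, for the CONSORT diagram: "This will also include numbers referred onto further specialist services during the study".

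**The concern.** Without randomisation, any difference between the two pairs of centres is also a difference between the arms. The protocol itself names one such difference, the timing and type of post-treatment care, and it recruits women at points along that pathway. It also gives a reason why timing could matter for the outcome: in describing the third discussion topic, it says that expectations about coming out-patient visits may heighten FCR.

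Every participant must enter with an FCR4 score of 10 to 14, so the arms will start at similar levels even if they are at different stages after treatment. A difference in stage would show in the later course of FCR, which is what the growth-curve analysis compares. If FCR changes at a different pace soon after treatment than later on, an imbalance in time since completion would look like a difference in slope. Likewise, without a description of routine contact, the control trajectory cannot be tied to a known level of usual care. Both matter because the article expects evidence on potential effectiveness and intends to use the data to design a randomised trial.

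**Working it through.** No stated figure decides this point, so the main check sets the sections side by side.

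1. **Can the arms differ in timing and support?** Trial design says care can vary between the four centres. Arm is two centres against two. The arms may differ; the text does not show that they do.
2. **Is recruitment linked to that timing?** Yes. Women are identified from appointment systems and approached before a follow-up visit or end-of-treatment review.
3. **Is time since completion named?** It is not in the screening list. That list is introduced by a word that leaves it open, and it also omits disease severity, which Quantitative analysis uses, so it cannot be read as complete. Among the three named covariates, treatment experience is undefined and is not clearly elapsed time.
4. **Does the 6-month window settle it?** It limits time since completion to 0 to 6 months but does not balance it between arms. It appears only in the Abstract. Applying it requires knowing when each woman finished treatment.
5. **Is support recorded?** In part. Referrals and offers of additional support are recorded, and numbers referred are reported. Ordinary nurse or clinic contact is not named.

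**Illustration of the stakes.** The shift b, in SD units, is an assumption; the documents give no value. Inputs from Sample size and Quantitative analysis: n = 65 per arm; 30% attrition, so 65 × 0.70 = 45.5 per arm; alpha 0.05 two-sided. With no intervention effect, an unadjusted two-sample z-test rejects with probability

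P = Φ(δ − 1.96) + Φ(−δ − 1.96), where δ = b / √(2/n).

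Example, b = 0.2 and n = 65: √(2/65) = 0.1754; δ = 0.2/0.1754 = 1.140; P = Φ(−0.820) + Φ(−3.100) = 0.206 + 0.001 = 0.207.

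| Assumed b (SD) | 65 per arm | 45.5 per arm |
|---|---|---|
| 0.1 | 8.8% | 7.6% |
| 0.2 | 20.7% | 15.9% |
| 0.3 | 40.2% | 29.9% |

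These rates ignore clustering. They show what a shift of a given size would do, not that such a shift exists.

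**The case against.** The strongest reply is that a journal article condenses the full protocol. Contents of baseline forms and full adjustment sets are commonly left to that document or to the analysis plan, and neither is shown. The screening list is open, and supplementary file 1 is not shown. The three covariates stand in the sentence on simulation for a future sample size, not in a closed list for the mixed or growth-curve models. All of this stands: it cannot be said that time since treatment will go uncollected or unadjusted. What remains is that, where the article does name covariates for the between-arm slope, it does not clearly include the variable most closely tied to the centre difference it declares.

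Three stronger readings are tempting and are not supported.

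- A reader might infer that women in the two arms will enter at systematically different times. Trial design says only that care can vary. Variation among four centres need not separate one pair from the other, and timing of support is not the same as timing of recruitment.
- A reader might infer that the data could not reveal such differences at all. Referrals and offers of support are recorded, and applying the 6-month window would need an approximate completion date.
- A reader might attach a size. A slope difference of 0.03 to 0.10 SD per month over 3 months gives 0.09 to 0.30 SD, or 18% to 60% of the planned effect of 0.5. But the rate is invented, and no gap in time since treatment between the arms is given to support it.

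It is also fair to say that the stated aim is feasibility and acceptability, and that the design and the variation in care are openly disclosed. That limits the consequence to the between-arm outcome comparison.

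**Conclusion.** The point holds as a modest, inexpensive improvement. Arm is determined by centre, and care after treatment can vary by centre in timing and type. The named covariates do not clearly include time since treatment ended, and routine contact is not named for collection. The FCR trajectory comparison could therefore be biased, in either direction, by an amount that the documents do not allow to be estimated.

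The conclusion assumes that treatment experience does not already mean elapsed time, and that documents not shown do not add the variable. If either assumption fails, the covariate part of the point falls away.

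The 6-month window in the Abstract and the eligibility criteria without a window are inconsistent and must be reconciled in any case.

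**What to change.** 1. Record the date of primary treatment completion at screening. The Abstract's window already calls for it. Reconcile the Abstract and Eligibility and recruitment on that window.
2. Tabulate time since completion by centre and by arm.
3. Add it as a covariate in the FCR, HADS and EQ-5D models and in the Monte Carlo model. In the growth-curve model let it predict the slope as well as the intercept, since a term for the starting level alone would not adjust the slope comparison.
4. Optionally, at the last follow-up in both arms, add one item on contacts with the breast team or support services other than the Mini-AFTERc call. Without that exclusion the item would count the intervention itself. Report it descriptively by centre and do not adjust for it, because contact after baseline may be affected by the intervention.
5. Report the between-arm comparison as exploratory.

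The cost is one date field, one covariate and, if the item is added, a small questionnaire burden. The adjustment draws on variation in time since completion within centres; if each centre recruits at one fixed point, it will achieve little, and the table in step 2 will show that. With two centres per arm, all other centre differences remain inseparable from the intervention.
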